#### Individual-Level Exclusion Criteria Applied to the Exposed and Referent Groups

We will exclude individuals who meet any of the following criteria:

Individuals prescribed drug B within 180 days before the cohort entry date (to ensure those in the exposed group are new users of drug B and that those in the referent group were not previously exposed).Individuals prescribed another medication in the same class as drugs A and B on the cohort entry date. For example, if drug A or B is sertraline, which is a serotonin reuptake inhibitor (SSRI), individuals prescribed a nonsertraline SSRI on the cohort entry date will be excluded.Individuals discharged from the hospital or emergency department within 2 days before the cohort entry date (to ensure that prescriptions are new outpatient prescriptions).Individuals whose day supplies for drug A or B are ≥100 days or <2 days.Individuals who are nonpermanent Ontario residents, are aged <66 or >105 years on the cohort entry date, or have a date of death on or before the cohort entry date (data cleaning exclusions).

An individual can only enter a cohort once; if an individual meets the eligibility criteria multiple times, the first eligibility date will serve as the cohort entry date.

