### Source Population

The source population will comprise adults aged 66 years and older who filled at least one oral outpatient drug prescription with a supply duration of at least 3 days, dispensed between July 1, 2002, and March 1, 2023 (codes for nonoral versions are provided in Multimedia Appendix 5). The age criterion will ensure that individuals in this population have at least 1 year of prior ODB prescription drug coverage.

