#### New Users of Drug B

From the sample of regular users of drug A, we will select individuals who start a prescription for a new medication (drug B) that is taken concurrently with drug A, meaning drug B’s start date is on the same date as the most recent drug A fill date or falls within drug A’s supply duration.

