#### Cohort Entry Dates for Exposed and Referent Groups

The exposed group will comprise regular users of drug A and new users of drug B, as described earlier. The cohort entry date for individuals in the exposed group will be the start date of drug B. The referent group will comprise regular users of drug A who are not coprescribed drug B. The cohort entry date for individuals in the referent group will be assigned based on the distribution of the time differences between the most recent prescription for drug A and the initiation of drug B for individuals in the exposed group, ensuring similar observation periods between groups [25].

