### Challenges and Limitations

Despite using advanced statistical techniques to control for confounding, residual confounding may still be present [51]. Factors that are not captured in the administrative data or that are measured with error could bias our results [52]. To address this, we will conduct multiple sensitivity analyses and use negative control outcomes to assess the robustness of our findings [37].

Our study focuses on acute (30-day) outcomes, which will not capture the effect of long-term exposure [53]; however, we will conduct additional analyses to assess longer follow-up times.

The study is designed to identify harmful DDIs with a moderate-to-high risk in magnitude in cohorts of at least 1000 individuals, and therefore, it will have limited statistical power to detect small risk increases.

Our study does not include data on nonprescription (over-the-counter) drugs, drugs prescribed in hospitals, or comprehensive outpatient prescription drug use in children or adults aged under 65 years. These exclusions may limit the generalizability of our findings to a broader population. However, the focus on older adults is justified, given their higher risk of polypharmacy and adverse drug interactions.

Given the large number of comparisons being made, there is a risk of spurious findings due to multiple testing [16]. To mitigate this, we will apply the Benjamini-Hochberg procedure to control the false discovery rate and use E-values to assess the robustness of our findings against unmeasured confounding [31].

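### The hospital-contact exclusion leaves in people still in hospital on the entry date, a state open to referents but nearly closed to the exposed; this lowers the RR and RD for mortality and probably ICU admission

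*Protocol article*

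**What the plan says.** In *Individual-Level Exclusion Criteria Applied to the Exposed and Referent Groups*, the one rule on hospital contact removes "Individuals discharged from the hospital or emergency department within 2 days before the cohort entry date (to ensure that prescriptions are new outpatient prescriptions". The only other check on a person's state at entry removes those who "have a date of death on or before the cohort entry date".

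The two groups get their entry dates differently (*Cohort Entry Dates for Exposed and Referent Groups*). For the exposed, "The cohort entry date for individuals in the exposed group will be the start date of drug B". For the others, "The cohort entry date for individuals in the referent group will be assigned based on the distribution of the time differences" between the last drug A fill and the start of drug B among the exposed. *New Users of Drug B* allows a zero lag: drug B may begin when its "start date is on the same date as the most recent drug A fill date", or later within drug A's supply.

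The prescriptions are outpatient ones: *Source Population* requires that people "filled at least one oral outpatient drug prescription with a supply duration of at least 3 days". *Challenges and Limitations* lists "drugs prescribed in hospitals" among the data the study does not have.

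**The concern.** The discharge rule looks back from a dispensing. Its stated purpose is to make sure the prescription is a new outpatient one, and that has no meaning for a referent whose entry date carries no prescription. A referent who fills drug A, is admitted, and is still in hospital on the assigned date meets no listed exclusion. Follow-up for that person starts in the middle of an acute admission. An exposed person could hardly start follow-up in that state.

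All-cause mortality is a prespecified outcome, ICU admission is on the outcome list, and both can occur during a stay already under way. If referent risk is raised in this way, a true harm is harder to see in a study built to find harms. Under *Criteria for Identifying Potential Signals of Harmful DDIs*, a cohort with no signal is not analysed further, so a masked harm never reaches the sensitivity analyses. As described, those analyses do not redefine referent entry, and the control period starting 90 days earlier cannot examine mortality.

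**Working it through.** The article states no inpatient share and no baseline mortality, so there is no figure to reproduce. The check has three steps.

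**1. Who can be an inpatient on day 0 under the written rules**

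| | Exposed | Referent, zero lag | Referent, positive lag |
|---|---|---|---|
| Entry date | Outpatient start of drug B | Drug A fill date | Assigned day, no fill required |
| Removed if discharged in the 2 days before | Yes | Yes | Yes |
| Removed if admitted earlier and still in hospital | No, but rare by design | No, but rare by design | No, and nothing prevents it |

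**2. Effect on mortality**

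Inputs, all assumed:
- h, the weighted share of referents in hospital at entry: 0.1% to 2%
- r0, 30-day mortality of referents in the community: 0.2% to 1%
- rh, 30-day mortality of referents in hospital: 5% to 15%

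Formulas, taking the exposed group to contain no inpatients:
- Referent risk = (1 − h)·r0 + h·rh
- Inflation = referent risk / r0
- Observed RR = true RR / inflation
- Understatement of the RD = h·(rh − r0)

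Middle case, h = 0.5%, r0 = 0.5%, rh = 10%:
- Referent risk = 0.995 × 0.5% + 0.005 × 10% = 0.548%
- Inflation = 1.095
- A true RR of 1.50 is seen as 1.37
- The RD is understated by 0.005 × 9.5% = 0.048 percentage points

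Range over r0 and rh for each h:

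| h | Inflation | True RR 1.50 seen as | RD understated by (points) |
|---|---|---|---|
| 0.1% | 1.00–1.07 | 1.40–1.49 | 0.004–0.015 |
| 0.5% | 1.02–1.37 | 1.09–1.47 | 0.020–0.074 |
| 1% | 1.04–1.74 | 0.86–1.44 | 0.040–0.148 |
| 2% | 1.08–2.48 | 0.60–1.39 | 0.080–0.296 |

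For comparison, the signal criteria require lower 95% limits of at least 1.33 for the RR and 0.1% for the RD.

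**3. Outcomes that need a new admission or emergency visit**

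Take an assumed community risk of 3% and h = 2%.
- If inpatients cannot have the event, referent risk is multiplied by 0.98 and a null RR reads 1.02.
- If 15% of them are readmitted within follow-up, referent risk is multiplied by 1.08 and a null RR reads 0.93.

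The direction is therefore not fixed for these outcomes, and the upward movement in the RR is small.

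**The case against.** Several points against the concern are sound and limit it.

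- **Other biases act too.** Exposed people enter when a clinician starts a new drug, often for a new illness; the Discussion's own example is an antibiotic for a urinary tract infection. Referents enter on an assigned day. That pushes RRs upward. A reader might infer that the study as a whole hides harms, but the article does not support a net direction. Only this component is established.
- **Not all acute outcomes.** A reader might also infer that every acute outcome is inflated among referents. Hospital admission, emergency visit and their composite need a new event. Sepsis, delirium and the like count only if dated after entry, and the article does not give the dating rule. If they are dated by admission, the current stay precedes entry.
- **Not only referents.** A prescription can be collected for an admitted patient. Zero-lag referents are largely protected. Positive lags must fall within drug A's supply, which is under 100 days, so the inpatient share depends on the pair and may be well below 1%.
- **No single bias factor.** With h = 1% and rh = 10%, the RR is multiplied by 0.3/0.397 = 0.76 if r0 is 0.3%, but by 1/1.09 = 0.92 if r0 is 1%.
- **Many cohorts are too small for it to matter.** At r0 = 0.3% and a true RR of 1.8, the median 583 new users give 583 × 0.54% ≈ 3 exposed deaths, below the six required for analysis. For an estimate of 1.8 to have a lower limit of 1.33, even with unlimited referents, 1/[ln(1.8/1.33)/1.96]² ≈ 42 exposed deaths are needed. That is about 42/0.54% ≈ 7,800 exposed people, against an upper quartile of 2130.
- **Unshown material.** The full covariate list is in Multimedia Appendix 2. The article's examples name prior-year hospitalizations, which do not separate a current stay from a past one and could raise or lower these people's weight. If inpatient status at entry were itself a covariate, such referents would get propensity scores near zero and little weight.

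None of this closes the gap. The exclusion list goes down to data-cleaning items and reads as complete, and it does not cover a person in hospital on day 0.

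**Conclusion.** The concern holds in a limited form. As written, the rules allow inpatients on day 0 among positive-lag referents and almost none among the exposed. For all-cause mortality, and probably ICU admission, this component raises referent risk and lowers the RR and RD. For other in-hospital events it does so only if they are dated within follow-up. For outcomes needing a new admission or emergency visit the effect may be slightly opposite.

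The size cannot be obtained from the article. The inflation of referent mortality, about 1.00 to 2.5, rests wholly on the assumed ranges and on inpatient status not being handled by the weights. It matters mainly in cohorts large enough to reach the signal thresholds. The change is worth making because it is cheap and because no planned analysis would recover a mortality signal lost this way.

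**What to change.** Extend the exclusion, in both groups and before propensity scores are estimated, to anyone in hospital or an emergency department on the cohort entry date (admitted on or before it and not discharged before it), in addition to those discharged in the 2 days before. State whether a discharge on the entry date itself is excluded; the present wording leaves that open. State also how an admission beginning on the entry date is treated, because excluding it in both groups drops any outcome event that starts that day.

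The cost is one sentence and one date comparison in CIHI-DAD and NACRS, which are already study databases. A small share of referents and very few exposed people would be lost. Reporting the number removed per group would show how large the problem was.

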### Outcomes

We will examine 74 outcomes within 30 days of cohort entry (Textbox 1). The outcomes were chosen using a prespecified analytic approach and considering the clinical significance of the outcomes and the observed rates in the study region [16]. Many of the algorithms used to identify these outcomes have been validated in previous studies and demonstrate high sensitivity and specificity [26-30]. Shorter and longer follow-up times for outcomes will be examined in additional analysis (see the *Additional Analysis to Characterize the Signals* section).

Final set of 74 clinically relevant outcomes (ordered alphabetically).

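### The enter-once, first-date rule leaves open where an A user who starts B later belongs: one reading loses exposed patients, the other selects referents on later non-use of B

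*Protocol article*

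**What the plan says.** Under Cohort Builds, every cohort contains both an exposed and a referent group. Under New Users of Drug B, the exposed are drawn from the pool of regular A users when they start B. Under Cohort Entry Dates for Exposed and Referent Groups, "The cohort entry date for individuals in the exposed group will be the start date of drug B", while "The referent group will comprise regular users of drug A who are not coprescribed drug B". No time window is attached to that referent condition. The referent date is "assigned based on the distribution of the time differences between the most recent prescription for drug A and the initiation of drug B" among the exposed; the article does not name the A fill that anchors it.

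The Individual-Level Exclusion Criteria apply to both groups. They remove "Individuals prescribed drug B within 180 days before the cohort entry date", which looks backward only, and then add the once-only rule: "An individual can only enter a cohort once; if an individual meets the eligibility criteria multiple times, the first eligibility date will serve" as the entry date. Follow-up is short: "We will examine 74 outcomes within 30 days of cohort entry". The article does not say which group takes a person who qualifies for both, or what happens when a referent starts B after entry. The Cox sensitivity analysis names death as its only censoring event.

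**The concern.** Take someone who uses A for a year without B and then starts B. This person can qualify as a referent during the year and as exposed at the B start. Both groups sit in one cohort and a person may enter it once, so one of two things must happen.

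- **First date prevails.** The person is a referent and never contributes the B start. The exposed group shrinks towards people with no earlier A-only date.
- **B starters are taken first.** The person is exposed, and the referents are those left over. Referent membership then depends on what happened after the referent entry date.

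The second reading is the more serious. People who die cannot start B later, so every death stays among the referents while some survivors are removed. Referent mortality is inflated and a harmful pair can be masked. Conversely, if an outcome leads to a B prescription, people with that outcome leave the referent group more often than others, and the RR rises with no drug effect. The article's own material makes this plausible: urinary tract infection or urine culture is one of the 74 outcomes, and antibiotics appear as example drugs B.

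**Working it through.** The article gives no bias figure on this point, so there is none to reproduce. Taken from the article: 30-day follow-up, a lower 95% bound for the RR of at least 1.33, about 3.8 million people, and the example cohort sizes. Assumed: a 30-day risk of p = 1%, and the later-B shares below.

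**Reading A: first date prevails.** Let q be the share of referents who start B within 30 days, exposed for half the window on average. Then observed RR = RR / [1 + 0.5q(RR − 1)].

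| True RR | q = 5% | q = 10% |
|---|---|---|
| 1.0 | 1.00 | 1.00 |
| 1.5 | 1.48 | 1.46 |
| 3.0 | 2.86 | 2.73 |

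The effect on the RR is a small attenuation. The main cost is lost exposed patients.

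**Reading B: B starters taken first.** Let s and t be the shares of A users without and with the outcome who later start B. Referent risk = p(1 − t) / [p(1 − t) + (1 − p)(1 − s)]. The RR is multiplied by p divided by that risk, roughly (1 − s)/(1 − t). Bias is upward when t exceeds s and downward when it is smaller.

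Outcomes that prompt B, true RR = 1:
- s = 20%, t = 50%: referent risk 0.005/0.797 = 0.63%, RR 1.59
- s = 10%, t = 40%: RR 1.50
- s = 5%, t = 50%: RR 1.89
- s = 20%, t = 30%: RR 1.14

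Death (t = 0), true RR = 1:
- s = 20%: referent risk 0.01/0.802 = 1.25%, RR 0.80
- s = 1%: RR 0.99

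With a true mortality RR of 1.8, the observed value is 1.50 at s = 17%, 1.34 at 26% and 1.19 at 34%.

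**How large might s be?** The Results give 128,762 patients for levothyroxine plus rosuvastatin and 197,057 for levothyroxine plus amoxicillin. I take these as exposed, because overlap exists only for them. They are 3.4% and 5.2% of 3.8 million. If 10–20% of that population used levothyroxine (an assumption), 17–34% and 26–52% of A users would start B. Some of these had no earlier A-only date, so s itself may be lower.

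**Simulation check.** I simulated 2 million A users over 24 months with no effect of B and about 20% starting B later. Under reading B the mortality RR was 0.80–0.82. The RR for a non-fatal event was 1.14 or 1.32 when the event raised B starts 5- or 10-fold for three months. With B status fixed at the referent date, across all scenarios run, null RRs were 0.98–1.02.

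**Against the signal rule.** A lower bound of 1.33 requires a standard error of ln(RR/1.33)/1.96. Counting only exposed-group variance, the exposed events needed are about 1/SE²:
- RR 1.59: 0.179/1.96 = 0.091, about 120 events, or 12,000 exposed at 1% risk
- RR 1.50: about 266 events, or roughly 27,000 exposed
- RR 1.89: about 31 events, or 3,100 exposed
- RR 1.14: can never pass

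The Results give a median of 583 new users per cohort and an upper quartile of 2130.

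**The case against.** The best defence is that the article nowhere says referents must never receive B. Its only dated B criterion for them looks backward, so B status could naturally be judged at entry. The rule about meeting criteria repeatedly might concern only repeated B starts or repeated A episodes. The cohort-building figure and the full protocol are not shown and may fix the order of assignment.

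That defence is fair on missing detail, and I do not count missing detail as the finding. It does not dispose of the stated rule. Judging B at entry is coherent only if a referent who later starts B may also enter as exposed, and one entry per person per cohort forbids that as written.

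Several stronger readings are tempting and are not supported:
- **All or most B starters were eligible referents earlier.** Regular use needs two A fills and B may start on the date of the latest fill, so a person starting B at the second fill may have no earlier referent date. No figure supports most.
- **RRs are biased in both directions whatever the reading.** Two-way bias belongs to reading B only.
- **False signals will be common.** Upward bias needs a large share of people with an outcome to receive one particular drug out of more than 500, and the 1.33 lower-bound rule stops it in most cohort sizes.

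The planned safeguards do not settle the matter. Calendar year and prior A use in the propensity score help with timing, not with selection on later B. Matching, bootstrap and Cox are not described as changing who is a referent. The negative-control period lies before entry and cannot examine death.

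**Conclusion.** The concern holds in limited form. The once-only, first-date rule is not reconciled with the two group definitions, and either way of applying it does worse than a simple alternative. Taking the first date costs exposed patients and causes slight attenuation, with a null RR unchanged. Taking B starters first conditions referents on the future: the mortality RR falls by about the share of A users who later start B, and null RRs for outcomes that prompt B reach about 1.1 to 1.9 in the cases shown.

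These sizes rest on assumed later-B shares and a 1% risk; the documents supply neither. The bias is near nil for mortality where few A users start B. It matters for common pairs and for outcomes that B treats. False signals would be confined to large cohorts. Masked mortality signals deserve equal weight, because pairs that show no signal receive no further analysis.

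**What to change.** Make three changes to the cohort-building text:

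1. Judge the referent condition of not being coprescribed B only on data up to the assigned entry date, whatever happens later, and name the A fill that anchors that date.
2. Replace the once-only rule with at most one referent entry and one later exposed entry per person in each cohort.
3. Cluster the robust variance on person in the RR and RD models.

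The protocol should also say how B starts during the 30 days are handled. If they are left in, the attenuation is small: a true RR of 2 becomes 1.99, 1.95 or 1.90 if 1%, 5% or 10% of referents start B in the window.

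The cost is a change to the cohort-building code and a few sentences, before the analysis planned for completion in fall 2026. The downside is that some people appear in both groups, which clustering addresses.

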#### Cohort-Level Exclusion Criteria

To ensure meaningful results, only cohorts with a minimum sample size of 1000 patients, with at least 200 individuals in the exposed group and 200 individuals in the referent group, will be considered for further analysis.

### Outcomes

We will examine 74 outcomes within 30 days of cohort entry (Textbox 1). The outcomes were chosen using a prespecified analytic approach and considering the clinical significance of the outcomes and the observed rates in the study region [16]. Many of the algorithms used to identify these outcomes have been validated in previous studies and demonstrate high sensitivity and specificity [26-30]. Shorter and longer follow-up times for outcomes will be examined in additional analysis (see the *Additional Analysis to Characterize the Signals* section).

Final set of 74 clinically relevant outcomes (ordered alphabetically).

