High-throughput computing and automated analytical pipelines have proven effective for detecting potential DDIs in large health care datasets in other countries, such as the United States. Previous studies by Bykov et al [14] and Leonard et al [15] have demonstrated that these methods can efficiently confirm known interactions and identify novel signals. However, these approaches have largely been limited to single-object drugs, specific outcomes, or nonrepresentative datasets (derived from a specific subset of the population, such as those with a certain type of insurance, rather than the entire population), which may restrict generalizability. Building on these advances, our study will use high-throughput computing to analyze Ontario’s population-based, linked administrative databases, which capture comprehensive prescription and outcome data across the province’s universal health care system. Using a population-based, new-user cohort design, we will systematically evaluate nearly 200,000 medication pairs among 3.8 million older adults—an effort that would be impractical with traditional methods. This approach will not only fill a critical gap by providing large-scale, real-world evidence in a Canadian context but also enhance generalizability, generate signals that could inform clinical decision-making once validated, and strengthen postmarketing pharmacovigilance efforts for older adults. To the best of our knowledge, this represents the first application of such an approach in Canada, leveraging the strengths of a universal health care setting to further enhance the generalizability and clinical relevance of detected DDI signals.

The cohort study is designed to mimic typical clinical scenarios, for example, an individual who has been taking digoxin for 7 months and is then newly prescribed sulfamethoxazole-trimethoprim to treat a urinary tract infection. In DDI studies, such scenarios are categorized as follows:

Precipitant triggered: Individuals initiate the object drug first, followed by the precipitant, with follow-up starting on the day the precipitant is initiated.Object triggered: Individuals initiate the precipitant first, followed by the object drug, with follow-up starting on the day the object is initiated.

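### Exposed follow-up starts at a new prescribing decision but referents need no clinical contact at entry, so visits, tests and illness tied to the reason for drug B can be counted as harms of the pair

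*Protocol article*

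**What the plan says.** Under Cohort Entry Dates for Exposed and Referent Groups, the exposed rule is "The cohort entry date for individuals in the exposed group will be the start date of drug B". The comparison group is defined by "The referent group will comprise regular users of drug A who are not coprescribed drug B", and its entry date is "assigned based on the distribution of the time differences between the most recent prescription for drug A and the initiation of drug B". That aligns time since the last A fill. It does not require a consultation, a new complaint or a new prescription on the assigned date.

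The Outcomes section then states "We will examine 74 outcomes within 30 days of cohort entry". No lag or entry-day exclusion is given. The Discussion (Summary), classifying interaction scenarios, describes the precipitant-triggered type "with follow-up starting on the day the precipitant is initiated". Textbox 1 lists any physician visit, emergency visits, chest X-ray, three CT outcomes, pneumonia, depression, gout, and UTI or urine culture. The same Discussion section gives as its typical case a digoxin user who "is then newly prescribed sulfamethoxazole-trimethoprim to treat a urinary tract infection".

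The individual-level exclusion nearest to this issue covers "Individuals discharged from the hospital or emergency department within 2 days before the cohort entry date".

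**The concern.** Starting a new outpatient drug usually follows a clinical decision about a complaint, a finding or a diagnosis. Exposed time zero sits on or just after that decision. Referent time zero does not correspond to any such event, although a referent may have a contact by chance. Events on or after entry that belong to the reason for B will then be more frequent in the exposed group even if A and B do not interact. They include the prescribing visit if it falls on the same day, follow-up visits, imaging, cultures, and the illness itself as it is coded over the next weeks. In the protocol's own example, the reason for starting B is also a listed outcome.

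At stake is the purpose of the screen. This is a systematic bias, so large cohorts make it more significant, and Benjamini-Hochberg correction does not protect against it.

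**Working it through.** **Outcome list.** Textbox 1 has 56 individual and 18 composite outcomes; 56 + 18 = 74, as stated. By my classification, 5 are visits or admissions and 16 are tests or diagnostic procedures (11 individual, 5 composites containing one), so 21 of 74. Six more are surgical procedures.

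**Safeguards, one by one.**
- Propensity score: uses 5 years of comorbidity, the prior year's health care use and 120 days of dispensing. An illness arising at entry is not in it.
- Discharge exclusion: covers hospital and emergency discharges in the 2 days before entry, not office visits or tests, and not the entry day.
- Cox model, 1:1 matching, bootstrap and E-value: same entry date, same type of referent.
- Negative-control exposure period: this does move time zero, to 90 days before entry. If it runs 30 days it ends 90 − 30 = 60 days before B starts, too early to see an illness arising at entry. The protocol would read a null result there as support for the signal.
- 7- and 14-day windows: also start at entry.
- E-value above 2: E = RR + √(RR(RR − 1)). RR 1.33 gives 1.99 and RR 1.34 gives 2.01. A signal whose lower bound is at least 1.33 has a larger point estimate, so on the point estimate this rule screens out almost nothing more.

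**Size for a pair with no interaction.** The protocol gives no event rates, so p0 and f are assumptions. p0 is the referent 30-day risk; f is the share of B starters who have the outcome because of the reason for B. Then p1 = p0 + f(1 − p0) and RR = p1/p0. SE(log RR) = √[(1 − p1)/(n·p1) + (1 − p0)/(n·p0)], and the lower bound is RR × exp(−1.96 SE). I take n = 583, the median number of new users in the initial cohorts (Results), and assume an equal effective referent size.

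Any physician visit:

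| p0 | f | p1 | RR | RD (points) | RR lower bound |
|---|---|---|---|---|---|
| 0.40 | 0.75 | 0.850 | 2.12 | 45.0 | 1.91 |
| 0.40 | 0.90 | 0.940 | 2.35 | 54.0 | 2.12 |
| 0.50 | 0.75 | 0.875 | 1.75 | 37.5 | 1.60 |
| 0.50 | 0.90 | 0.950 | 1.90 | 45.0 | 1.75 |
| 0.60 | 0.75 | 0.900 | 1.50 | 30.0 | 1.40 |
| 0.60 | 0.90 | 0.960 | 1.60 | 36.0 | 1.49 |
| 0.70 | 0.75 | 0.925 | 1.32 | 22.5 | 1.25 |
| 0.70 | 0.90 | 0.970 | 1.39 | 27.0 | 1.31 |

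Worked row (0.60, 0.75): SE = √[0.1/(583 × 0.9) + 0.4/(583 × 0.6)] = 0.0365, so the lower bound is 1.50 × exp(−0.0716) = 1.40 and z = 0.405/0.0365 = 11.1. The RD lower bound is 30 − 1.96 × 2.38 = 25.3 points, far above 0.1%. With f = 0.50 the RR lower bounds at p0 = 0.40, 0.50 and 0.60 are 1.56, 1.37 and 1.23, so the last fails.

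Test or diagnosis outcomes, smallest f that passes both the RR and RD thresholds (2130 is the upper quartile of cohort size; 128,762 is the levothyroxine-rosuvastatin cohort):

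| p0 | n = 583 | n = 2130 | n = 128,762 |
|---|---|---|---|
| 2% | 3.3% | 1.9% | 0.8% |
| 5% | 5.5% | 3.6% | 2.0% |

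These shares address the thresholds only. At p0 = 2% and n = 583 the minimum case has z = 0.953/0.340 = 2.8, so the multiplicity correction may demand a larger f there. At n = 128,762 it has z of about 13.

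With f = 0 the model returns RR = 1.00 and RD = 0.

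**The case against.** Several points on the other side stand.

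- A reader might infer that everything that prompted B is counted. It is not: events before B's start date fall outside the window. What remains is same-day contacts and the subsequent work-up and course.
- The article does not say whether entry-day events count. The Discussion sentence on when follow-up starts describes scenario types rather than a counting rule, and the definitions sit in appendices not shown. Entry-day counting is implied, not established. The later course of the indication does not depend on it.
- Diagnoses such as pneumonia or depression may be identified from hospital or emergency records. If so, an office diagnosis that led to B would not count, and the bias is smaller for those outcomes. It is clearest for physician visits and tests.
- Not every B start is for an acute problem; the Results include chronic-chronic pairs.
- A reader might infer that such signals survive the whole process. The documents do not support that. Steps 2 to 6 review biological plausibility, interaction checkers, monographs and epidemiology, with two reviewers, and unsupported signals are dismissed. The bidirectional comparison also helps: reversing the order changes the drug started and its indication, so an indication-driven signal need not replicate. It only highlights concordant pairs, however, and the evidence review comes after Step 1 and does not correct the estimates.
- The limitations section concedes residual confounding, but only in general terms.

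**Conclusion.** The point holds in this form: the entry-date rule, the untreated referent and the outcome list together let indication-driven events be counted as harm. None of the listed sensitivity analyses is aimed at that, so such signals can pass Step 1.

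The size rests on assumed rates. For any physician visit, referent risks of 40-60% and 75-90% of starters with a counted contact give RR 1.50-2.35 and lower bounds of 1.40-2.12 at 583 per group. The claim that any large cohort would exceed 1.33 is not supported. At 70% referent risk the lower bound is 1.25-1.31 and fails at that size (at 2130 per group with f = 0.90 it is 1.35 and passes). Above 75% referent risk the RR cannot exceed 1/0.75 = 1.33. The direction and mechanism follow from the protocol text; how often it happens cannot be derived from it.

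**What to change.** 1. State the entry-day rule and count outcomes from day 1 in both groups.
2. Add to the sensitivity and bias analyses a lagged rerun for every signal, dropping the first days (for example days 0-2) in both groups. State how people whose event falls in those days are handled.
3. Flag, rather than delete, signals that do not persist, because a true immediate reaction could fail the lagged run.
4. Keep the prespecified visit and test outcomes. Making them ineligible would be a trade-off that the documents do not force. Label signals on them, and on outcomes that are a common indication for B, as prone to indication bias.
5. State that the lag removes only part of the bias: work-up and illness course after day 2 remain, and the referent still has no required contact.

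The cost is a date shift and one extra regression per signal, plus the loss of true same-day events from the main count. That loss should be acknowledged.
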